### Data collection and management

Data will be collected on case report forms by investigators at baseline visit, treatment visit, and follow-up visit. During treatment period, data will be collected through patient diary. Reports of laboratory findings will also be collected and recorded. For participants who withdraw from the trial, the investigator will contact the participants as much as possible to obtain all measurable outcome data. Every investigator should collect and record the data carefully to guarantee its accuracy. Data will then be entered into EpiData manager by two investigators independently and checked to ensure the accuracy. Personal information of participants will be kept confidential. Every participant will be assigned a participant number, and all data will be identified using this number, instead of directly displaying personal information. All research documents will be saved for at least 5 years after the end of the trial.

### Statistical analysis

Statistical analysis will be performed using SAS 9.2 software, with a statistical significance of *p* value less than 0.05. Normally distributed continuous variables will be described using mean ± standard deviation (SD), and non-normally distributed continuous variables will be described using median and interquartile range (IQR). Categorical variables will be described using frequencies and percentages. Primary outcomes will be analyzed according to the intention-to-treat principle. Intra-group differences of continuous variables will be tested for significance using paired-samples *t* test when the data is normally distributed, and will be tested using non-parametric test when the data is non-normally distributed. Between-group differences of continuous variables will be tested for significance using independent-samples *t* test when the data of the two groups are normally distributed and have equal variance, and will be tested using non-parametric test when the data of the two groups are non-normally distributed or have unequal variances. Chi-square test will be used for categorical data. Data from participants who drop out from this study will be implemented by the last-observation-carried-forward (LOCF) method. Interim analyses will not be performed. For the co-primary endpoints, Bonferroni correction will be performed to correct multiplicity.

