### Study process

#### Baseline visit

After signing an informed consent, patients will be interviewed to obtain information on demographic characteristics, history of past and present illness, and current medications. General physical examination (including height, weight, blood pressure, respiratory rate, heart rate, and temperature) and laboratory tests (including serum uric acid and C-reactive protein) will be conducted. Degree of joint pain, swelling, redness, and mobility will be scored, and width and thickness of affected joints will be measured. Patients who meet the eligibility criteria will be randomly assigned to treatment group and control group, with 103 patients in each group. Investigators will also instruct participants on how to score the degree of joint pain, swelling, redness and mobility, and how to measure the width and thickness of joints.

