#### Placebo group

In order to evaluate the absolute efficacy and safety of Qingpeng ointment for AGA and reduce the risk of bias, we chose placebo as comparison. Participants in control group will be treated with placebo ointment (produced by Tibet Cheezheng Tibetan Medicine Co., Ltd). The ingredients of placebo ointment include purified water, liquid paraffin, glycerinum, methylparaben, and food coloring. The placebo ointment is the same as Qingpeng ointment in texture, color, smell, and packaging. The usage of placebo ointment is the same as Qingpeng ointment.

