#### Rescue medicine

DSSRT (produced by Beijing Novartis Pharmaceutical Co., Ltd; specification: 75mg/tablet, 10 tablets/box) will be given to participants in both treatment group and control group as rescue medicine. Patients in both groups are recommended to take the rescue medicine only when the VAS score of joint pain is ≥ 7 points (scale of 0 to 10), which is scored by patients themselves. Patients will also be recommended not to take the rescue medicine when joint pain is reduced to a tolerable extent (VAS score reduce to less than 7 points). The recommended dose is one tablet per time, once daily, and the maximum dose is one tablet per time, twice a day.

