### Outcomes

#### Primary outcomes

Because the objective of this study is to investigate the efficacy of Qingpeng ointment for relieving pain and swelling of joints in patients with AGA, changes in joint pain severity (measured using VAS), joint swelling degree (measured using VAS), and width and thickness of affected joints (measured using vernier calipers) between baseline and treatment completion will be considered as the primary outcomes.Joint pain: Degree of joint pain will be measured by participants, using a visual analogue scale (VAS, 0–10 points, 0=no pain, 10=intolerable pain), at baseline, every day during treatment, and after 7-day treatment.Joint swelling:2.1 The width and thickness of each affected joint will be measured using vernier calipers (brand: Ruineng, model: NR0139) at baseline, every day during treatment, and after 7-day treatment.2.2 Degree of joint swelling will be measured by participants, using a visual analogue scale (VAS, 0–10 points, 0=no swelling, 10=intolerable swelling), at baseline, every day during treatment, and after 7-day treatment.

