### Sample size estimation

This study includes two primary outcomes: joint pain and joint swelling. Sample size was estimated based on these two primary outcome measures. Estimation according to joint pain was based on results from a previous study [23]. In this study, 47% participants in treatment group (Qingpeng ointment plus diclofenac sodium tablets) had significant relief of joint pain (the score of joint pain degree measured by a self-developed scale reduced by 6 points), and 25% participants in control group (diclofenac sodium tablets) had significant relief of joint pain. On the basis of a 5% type I error rate (*α*=0.05) and a power of 90% (*β*=0.1), the sample size of each group was 82. Assuming a 20% dropout rate, a total of 206 participants should be recruited, with 103 participants in each group.

Estimation according to joint swelling was likewise based on results from another previous study [19], which established score of joint swelling measured by a 0–3 points scale as 0.45 points after receiving Qingpeng ointment plus etoricoxib tablets, and the estimated standard deviation is 0.37. Score of joint swelling after receiving vaseline plus etoricoxib tablets is 0.87, and the estimated standard deviation is 0.64. On the basis of a 5% type I error rate (*α*=0.05) and a power of 90% (*β*=0.1), the sample size of each group was 27. Assuming a 20% dropout rate, a total of 68 participants should be recruited, with 34 participants in each group.

Based on these results, we chose the larger sample size of 206 participants, with 103 participants in each group.

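### The primary changes from baseline are to be compared by an unadjusted t test or non-parametric test; ANCOVA on each outcome's own baseline, already collected, would be generally more precise and would keep one mean difference as the effect.

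*Protocol article*

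**What the plan says.** Under Primary outcomes, the protocol article states that changes in pain VAS, swelling VAS, and width and thickness of affected joints "between baseline and treatment completion will be considered as the primary outcomes".

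The baseline of each of these is recorded before randomisation. Under Baseline visit: "Degree of joint pain, swelling, redness, and mobility will be scored, and width and thickness of affected joints will be measured".

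The Statistical analysis section names the between-group method. The first branch reads "Between-group differences of continuous variables will be tested for significance using independent-samples" *t* test, for groups that are normal with equal variances. Otherwise the comparison "will be tested using non-parametric test when the data of the two groups are non-normally distributed or have unequal variances". The non-parametric test is not named, and no covariate appears. The same section adds LOCF for dropouts and "For the co-primary endpoints, Bonferroni correction will be performed to correct multiplicity".

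**The concern.** The article does not leave the primary test open. It states one, and an analysis plan that used ANCOVA would depart from this text.

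A change score does use the baseline, but it subtracts all of it. When baseline and day 7 are only partly correlated, the best slope is usually below 1. Subtracting the whole baseline then over-corrects any chance imbalance (regression to the mean) and adds variance. With a Bonferroni correction each primary test runs at a stricter level, so lost precision costs power. Here the precision could be recovered without recruiting anyone.

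The switch to a non-parametric test is the second issue. If it is triggered, the primary analysis changes from a difference in mean change to a comparison of distributions, on the strength of the data. The planning figures for swelling make the trigger plausible. The SD after the ointment was 0.37, while for the control "Score of joint swelling after receiving vaseline plus etoricoxib tablets is 0.87, and the estimated standard deviation is 0.64". The variance ratio is (0.64/0.37)² = 2.99. Those are post-treatment scores on a 0–3 scale, so this is only an indication for VAS changes.

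**Working it through.** **What the plan's own figures contain.** The sample sizes reproduce at a one-sided 5% level with 90% power, using (1.645 + 1.282)² = 8.56 (the article does not state the sidedness).
- Pain, 47% against 25%: 8.56 × 2 × 0.36 × 0.64 / 0.22² = 81.5, so 82 per group; 82/0.8 gives 103.
- Swelling, 0.45 against 0.87: 8.56 × (0.37² + 0.64²) / 0.42² = 26.5, so 27 per group; 27/0.8 gives 34.

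The first rests on a responder proportion and the second on a post-treatment score. Neither gives an SD of VAS change or a baseline/day-7 correlation, so the quantities below are assumptions shown over a range.

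**Formulas.** Let s0 and s1 be the baseline and day-7 SDs and r their correlation. The treatment difference has per-patient variance
- change score: s0² + s1² − 2·r·s0·s1
- ANCOVA: s1²(1 − r²)

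The ratio of ANCOVA to change score is at most 1. It equals 1 only when the slope r·s1/s0 is 1. With equal SDs it is (1 + r)/2.

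**Variance ratios.**

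| s0, s1 | r = 0.2 | r = 0.4 | r = 0.6 |
|---|---|---|---|
| equal | 0.60 | 0.70 | 0.80 |
| 1.5, 2 | 0.76 | 0.87 | 0.97 |
| 2, 1.5 | 0.43 | 0.49 | 0.54 |

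For caliper sizes, anatomy probably dominates. Assuming equal SDs and r = 0.9, the ratio is 0.95. When s1 is 1.25 times s0 and r = 0.8, the slope is 1 and the ratio is 1.00, so there is no gain.

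**What this means for 103 per arm, equal SDs.**
- Equivalent size under the change-score test: 103/0.80 = 129 and 103/0.60 = 172 per arm.
- 95% half-width in SD units. Change score: 1.96·√(2(1 − r))·√(2/103) = 0.345 at r = 0.2 and 0.244 at r = 0.6. ANCOVA: 1.96·√(1 − r²)·√(2/103) = 0.268 and 0.218.
- Chance imbalance: the 95% limit at baseline is 1.96·√(2/103) = 0.27 SD. The change score over-corrects by (1 − r) times this, which is 0.22 SD at r = 0.2 and 0.11 SD at r = 0.6.

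**Power.** Take an effect at which the change-score test has 80% power; the 80% is a reference point and not a figure from the article. At two-sided 0.025 (Bonferroni for two outcomes), ANCOVA has Φ((2.241 + 0.842)/√0.80 − 2.241) = 88.6%, and 95.9% at ratio 0.60. At 0.0125 (four outcomes) the figures are 89.2% and 96.5%.

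**Check by simulation.** With 82 per arm, a true effect of −0.40 SD and 4,000 trials per case, both estimators averaged about −0.40. The variance ratios were 0.65, 0.74 and 0.87 for r = 0.3, 0.5 and 0.7, against 0.65, 0.75 and 0.85 from theory.

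**The case against.** The strongest reply is that nothing here is wrong. The t test is pre-stated, valid and unbiased, and it already refers to baseline. That stands: this is a point about efficiency and about the stability of the estimated effect. A reader might infer from the missing covariate that the planned result would be biased. The documents do not support that, because randomisation protects the unadjusted comparison.

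The size of the gain is assumed. That stands too. The ratio runs from 0.43 to 0.97 over the cases shown, and LOCF from early diary days would probably raise r for dropouts and shrink the gain further.

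On the only continuous planning inputs, power is ample in any case. Take swelling at 0.45 against 0.87 with SDs 0.37 and 0.64, 82 per arm, equal baseline and day-7 SDs within each arm, and r = 0.2. The change-score standard error is √(1.6 × (0.37² + 0.64²)/82) = 0.103. Power is about 97% at two-sided 0.025 and 94% at 0.0125. At r = 0.6 it exceeds 99.9% at 0.025. ANCOVA adds at most 6 points. This is fair for swelling if a post-treatment 0–3 score is a guide to VAS change, but even then the confidence interval narrows. For pain the article plans on responder proportions only, so power for mean VAS change cannot be derived.

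A last reply is that covariates belong in an analysis plan that is not shown. That carries less weight here, because the article names the between-group test itself.

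**Conclusion.** The point holds as a recommended improvement. The t-test branch is sound but generally less precise than ANCOVA, which targets the same mean difference. For the pain and swelling VAS the variance would fall by about 20 to 40%, assuming equal SDs and r of 0.2 to 0.6. For width and thickness the gain is probably about 5%. It disappears where the baseline slope is near 1.

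Two stronger readings should be avoided. First, a reader might infer that ANCOVA estimates the same effect as the whole stated procedure. That is so only for the t test; the non-parametric branch gives no mean difference, so replacing it changes what is estimated. Second, because diclofenac is allowed "only when the VAS score of joint pain is ≥ 7 points (scale of 0 to 10), which is scored by patients themselves", a reader might fault the aim stated under Placebo group, "In order to evaluate the absolute efficacy and safety of Qingpeng ointment for AGA". That is a preference about wording. Rescue in both arms is disclosed in the Abstract and under Treatment period, Rescue medicine, Allocation concealment and blinding, and Discussion, and remaining rescue tablets are a secondary outcome.

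**What to change.** In the Statistical analysis section, before unblinding:

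1. Make the primary between-group analysis of each primary outcome an ANCOVA with that outcome's own baseline as covariate: pain VAS on baseline pain, swelling VAS on baseline swelling, width on baseline width, thickness on baseline thickness. The treatment coefficient is the same whether change or the day-7 value is modelled, so the outcome definition need not change. Where several joints are measured, use the same patient-level summary at both times.
2. Use heteroscedasticity-robust standard errors, so that unequal variances do not force a change of test.
3. Keep the Bonferroni correction.
4. Keep the stated t or non-parametric test as a sensitivity analysis.

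No new data or visits are needed. The cost is an amendment, which the Ethics section sends to each centre's ethics committee and to the registry. The model assumes a roughly linear relation to baseline, and the return is small where the slope is near 1.

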### Study setting

This study will be conducted in three hospitals: Fangshan Hospital, Beijing University of Chinese Medicine in Beijing; the Second Affiliated Hospital of Zhejiang Chinese Medical University in Hangzhou, Zhejiang Province; and Liuzhou People’s Hospital in Liuzhou, Guangxi Zhuang Autonomous Region.

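### The primary between-group test is picked from the observed data and moves to a rank test when variances differ; one baseline-adjusted model fixed in advance would be sounder and more efficient

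*Protocol article*

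**What the plan says.** The Statistical analysis section of the protocol article gives a two-branch rule for between-group comparisons of continuous variables. The independent-samples t test applies when both groups are normal and share a variance. Otherwise the comparison "will be tested using non-parametric test when the data of the two groups are non-normally distributed or have unequal variances". The two triggers are joined by *or*, so unequal variances alone are enough. No unequal-variance t test and no covariate is named.

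The Primary outcomes section defines the primary variables as changes from baseline to the end of treatment in pain VAS, swelling VAS, and joint width and thickness. Baseline values are collected at the baseline visit.

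The only SDs for a continuous outcome are in Sample size estimation, from an earlier study of swelling on a 0–3 scale: "0.45 points after receiving Qingpeng ointment plus etoricoxib tablets, and the estimated standard deviation is 0.37" and "Score of joint swelling after receiving vaseline plus etoricoxib tablets is 0.87, and the estimated standard deviation is 0.64".

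**The concern.** Three things follow from the rule as written.

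- **The remedy does not match the problem.** A rank-sum test is not a test of equal means when the two distributions differ in spread. If they are also skewed, it can reject although mean changes are equal. Unequal variance has a direct remedy, the Welch test or robust standard errors, and the rule passes over it.
- **The hypothesis depends on the data.** One primary outcome may end as a comparison of means and another as a comparison of rank ordering, according to preliminary checks. What the trial estimates for each outcome is then not settled beforehand.
- **Baseline is used inefficiently.** Subtracting it is legitimate, but for a given number of patients a change-score comparison is usually less precise than a model with baseline as a covariate.

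At stake are the interpretation of the primary result and some precision.

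**Working it through.** **Inputs.** SDs 0.37 and 0.64, means 0.45 and 0.87, 5% type I error, 90% power, and 27 (swelling) and 82 (pain) per group before dropout, all from Sample size estimation. Assumed, because the document does not give them: an F test as the variance check, the shape of the distributions, the baseline SD, and the baseline-to-day-7 correlation r. All rejection rates below are at a two-sided nominal 5%.

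**1. The plan's own figure.** Pooled SD = √[(0.37² + 0.64²)/2] = 0.523; difference = 0.87 − 0.45 = 0.42. Then n = 2 × [0.523 × (1.645 + 1.282)/0.42]² = 26.5, so 27 per group. This matches the stated 27 with a one-sided 5% level; a two-sided level gives 33. Sidedness is a separate matter. The match shows that these are the SDs the plan used.

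**2. Would these SDs trigger the switch?** Variance ratio = (0.64/0.37)² = 2.99. For normal data with that ratio, an F test declares unequal variances with probability 78% at 27 per group and 99.8% at 82.

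**3. What the rank test then does when means are equal.** Simulation, 82 per group:

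| Scenario | Rank-sum rejects | Welch rejects |
|---|---|---|
| Normal, SDs 0.37 and 0.64 | about 6% (5.6–5.9% across runs) | 5.1% |
| Gamma, both means 0.66, same SDs | 38–39% | about 5% |
| Gamma, both means 0.87, same SDs | 25–26% | about 5% |
| Gamma, both means 0.66, each arm keeping its own SD/mean ratio | 6.4% | 5.0% |
| Both arms from one distribution | 5.0% | about 5% |

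The SD/mean ratios in the fourth row are 0.37/0.45 = 0.82 and 0.64/0.87 = 0.74.

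**4. Moving to change scores.** The SDs above are for post-treatment scores, whereas the trial tests changes. Subtracting an independent normal baseline from the gamma scores (mean 0.66) lowers the rank-sum rejection rate to about 15%, 8% and 5% for an assumed baseline SD of 0.3, 0.5 and 0.8. The variance check then triggers about 62% of the time at 0.5 and 28% at 0.8. Welch stays at about 5%.

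**5. Power cost of the rule.** For normal data with SDs 0.37 and 0.64, an illustrative difference of 0.25 and 82 per group, power is 85.9% with Welch and 83.9% with the switching rule, a loss of 2 points.

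**6. Baseline adjustment.** With equal variance σ² at both times, the change score has variance 2σ²(1 − r), and ANCOVA has residual variance σ²(1 − r²). The ratio is (1 − r²)/[2(1 − r)] = (1 + r)/2:

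| Assumed r | Variance ratio | Saving in patients |
|---|---|---|
| 0.3 | 0.65 | 35% |
| 0.5 | 0.75 | 25% |
| 0.7 | 0.85 | 15% |
| 0.9 | 0.95 | 5% |

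**The case against.** The strongest reply is that the harm is small or hypothetical, and much of it stands.

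- **The plan's own SDs make the test wrong.** A reader might infer this, but the document does not support it. With those SDs and normal data the rank test rejects about 6% instead of 5%. The 38% also needs skewness and an ointment that changes spread without changing the mean. In the source figures the larger SD goes with the larger mean. If each arm keeps its own SD/mean ratio, rejection is 6.4%; if the ointment does nothing, it is nominal.
- **The switch is near certain.** The 99.8% belongs to a post-treatment score on a 0–3 scale in a study with etoricoxib in both arms. No SD is given for change on the 0–10 VAS or the calipers.
- **Baseline is discarded.** It is subtracted, and the comparison is valid under randomization. Covariate adjustment improves efficiency; it does not correct an error.
- **Adjustment would rescue the power.** One can compute 76% power for 47% against 25% responders at 82 per group and two-sided 0.025, and apply the variance ratio. But that is a responder comparison ("47% participants in treatment group (Qingpeng ointment plus diclofenac sodium tablets) had significant relief of joint pain"), not a change-score test, so it can only illustrate.
- **Centre must be in the model, and paired tests will be read as efficacy.** The protocol states "This study will be conducted in three hospitals", but the Randomization section names no stratification by centre. Nothing says the within-group tests will serve as evidence of efficacy.

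A rank test can also be accompanied by a shift estimate in VAS points, and a condensed article may leave covariates and the name of the rank test to the full plan. What remains is the switching rule itself, which the article states in full: it is fixed, and fixed badly.

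**Conclusion.** The point holds in a limited form. The rule selects the primary test from the observed data and sends unequal-variance data, even when normal, to a test that does not address equal mean change.

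The size error is small for normal data: about 6% against 5% with SDs 0.37 and 0.64. It becomes large only if the data are also skewed, with about 5% to 38% across the assumed scenarios at 82 per group. Skewness is plausible for a score bounded at zero whose mean is only 1.2 to 1.4 SDs above it, but it is an assumption. How often the switch would occur in this trial cannot be known from the document. Welch held close to 5% in every scenario examined, so nothing is gained by leaving it out.

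The unadjusted comparison of changes is valid. It forgoes between 35% and 5% of variance for assumed r between 0.3 and 0.9, given equal variances at the two times. This is a worthwhile improvement to the plan, not a threat to the trial's validity.

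**What to change.** For each primary outcome, name one primary method before unblinding: ANCOVA of the day-7 value on treatment and baseline value, with heteroscedasticity-robust standard errors, reporting the adjusted mean difference and its confidence interval. Using the change instead of the day-7 value gives the same treatment estimate once baseline is in the model. Remove the normality and variance checks as a selector of the test. Keep a rank test as a sensitivity analysis. A centre term is optional. If the team prefers an unadjusted comparison, the Welch test on the changes removes the switching problem but not the inefficiency.

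The cost is analysis wording only: the baseline values are already collected, no visit or measurement is added, and the Ethics section already describes how amendments are approved and registered.

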#### Treatment period

Patients in the treatment group will be treated with Qingpeng ointment, and patients in the control group will be treated with placebo ointment. Patients in both groups will be given diclofenac sodium sustained-release tablets (DSSRT) as rescue medicine. Drugs for other underlying diseases such as antihypertensive drugs, hypoglycemic drugs, and hypolipidemic drugs are permitted to be taken during the treatment period. And other Chinese patent medicine are prohibited during the trial. When participants experience severe skin allergies at application site, or experience serious adverse events, investigators will advise them to discontinue using the study drug. The degree of joint pain, swelling, redness, and mobility will be scored and recorded on patient diary every day by patients, and the width and thickness of affected joints will also be measured and recorded every day by themselves. The course of treatment is seven days.

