#### Withdrawal or dropout criteria

Participants will withdraw from this study in the following cases:Deciding to withdraw by themselvesNo longer continuing to use the study drugs or accept visitsHaving severe allergic reaction at the administration siteExperiencing serious adverse events or complications

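### LOCF is the only stated method for dropouts, although flare symptoms are expected to fall over the 7 days; the Day-7 comparison is biased if dropout rate or timing differs by group

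*Protocol article*

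**What the plan says.** All references are to the protocol article.

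- **Statistical analysis**, missing data: "Data from participants who drop out from this study will be implemented by the last-observation-carried-forward (LOCF) method". No exception and no second method is given.
- **Statistical analysis**, analysis principle: "Primary outcomes will be analyzed according to the intention-to-treat principle".
- **Primary outcomes**: changes in pain VAS, swelling VAS and joint width and thickness "between baseline and treatment completion will be considered as the primary outcomes". Each is measured "at baseline, every day during treatment, and after 7-day treatment".
- **Treatment period**: symptom scores "will be scored and recorded on patient diary every day by patients", and patients also take the caliper measurements daily.
- **Data collection and management**: "For participants who withdraw from the trial, the investigator will contact the participants as much as possible to obtain all measurable outcome data".
- **Withdrawal or dropout criteria**: the list includes participants no "longer continuing to use the study drugs or accept" visits, and those with a severe local allergic reaction or a serious adverse event.
- **Sample size estimation**: 20% dropout is assumed.

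**The concern.** LOCF assumes that a patient's score stays where it was on the last day recorded. In a flare enrolled within a week of onset and followed for 7 days, the expected course is improvement. A patient last seen on Day 2 is then given a Day-7 score that is probably too high, and one last seen on Day 6 a score that is nearly right. The error depends on when people leave, so it cancels under no effect only if rate and timing are alike in the two groups.

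The article describes two ways in which they might not be. A severe skin reaction at the application site is a withdrawal reason, and would fall mainly on the ointment group. The Discussion says very severe pain under topical treatment alone may affect compliance; if the ointment works, that would fall mainly on placebo. The first pattern would hide a benefit and the second would create or enlarge one. LOCF also enters the filled-in values as though they had been observed.

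Separately, the article promises to pursue outcomes after withdrawal, but the analysis section does not say whether a retrieved value replaces the carried-forward one.

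**Working it through.** **1. The article's dropout figure.** 82 / (1 − 0.20) = 102.5, rounded up to 103 per group, as stated. About 103 × 0.20 ≈ 20 participants per group could therefore have a carried-forward Day-7 value.

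**2. Inputs not in the article (assumptions).** No VAS trajectory, VAS SD, dropout day or dropout by group is given. Assumed: mean pain VAS falls exponentially from 6 to 1.5 over 7 days, identically in both groups (no true effect); leavers follow the average course; SD 2.

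**3. Overstatement per leaver.** VAS(t) = 6 × (1.5/6)^(t/7).

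- Day 2: 4.04, so 4.04 − 1.5 = 2.54 points too high.
- Day 3: 3.31, so 3.31 − 1.5 = 1.81 points too high.

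**4. Spurious group difference.** (placebo dropout − ointment dropout) × overstatement per leaver. Type I error is from simulation with 103 per group and a two-sided t test at 5%.

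| Dropout, placebo vs ointment | Last score | Spurious difference | Type I error |
|---|---|---|---|
| 25% vs 15% | Day 3 | 0.10 × 1.81 = 0.18 | about 10% |
| 25% vs 15% | Day 2 | 0.10 × 2.54 = 0.25 | about 13% |
| 30% vs 10% | Day 3 | 0.20 × 1.81 = 0.36 | about 23% |
| 30% vs 10% | Day 2 | 0.20 × 2.54 = 0.51 | about 37% |
| 20% vs 20% | same day | 0 | about 5% |

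Swapping the dropout rates between the groups reverses the sign.

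**5. Yardstick.** Detectable difference with 82 per group, SD 2, two-sided 5%, 90% power: (1.960 + 1.282) × 2 × √(2/82) = 1.01 points.

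**6. Different timing at equal rates, with a linear decline instead.** Suppose 20% leave each group, with last scores at Day 2 on placebo and Day 4 on ointment. The spurious difference is 0.20 × slope × [(7 − 2) − (7 − 4)] = 0.40 × slope. Slopes of 0.3, 0.5 and 0.7 points per day give 0.12, 0.20 and 0.28 points, with type I error of about 7%, 10% and 13%.

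**7. Dilution of a true effect when rate and timing match.** Assume slopes of 0.60 (ointment) and 0.45 (placebo). The true Day-7 difference is 7 × 0.15 = 1.05. If 20% leave each group at Day 2, the mean day used is 0.8 × 7 + 0.2 × 2 = 6.0, and LOCF estimates 6.0 × 0.15 = 0.90.

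**8. The two passages on withdrawn participants, side by side.** Data collection and management says "the investigator will contact the participants as much as possible to obtain all measurable outcome data". Statistical analysis applies LOCF to data from those who drop out. One reading is that LOCF fills only what is still missing after retrieval. The other is that everyone classed as a dropout gets the carried-forward value. The text does not choose between them.

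**The case against.** The size of the bias rests wholly on assumptions. The article's one dropout figure is 20% overall. With equal rate and timing the bias under no effect is zero. The milder imbalance produces at most a quarter of the detectable difference, and the larger one needs a threefold difference in dropout. The two mechanisms act in opposite directions and may partly offset, and rescue medicine is supplied partly to reduce dropout. Patients who leave because they are doing badly might not recover to the group average, so the overstatement per leaver could be smaller than shown. All of this stands. It limits what can be said about size, not the fact that the rule depends on dropout pattern.

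Three stronger readings are tempting, and the article does not support them.

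- A reader might infer that data retrieved after withdrawal will be discarded. The article does not say so. A retrieved Day-7 value could itself count as the last observation. What can be said is that precedence is unstated.
- A reader might infer that LOCF contradicts the intention-to-treat statement. It does not: dropouts stay in the analysis in their randomised group.
- A reader might infer from the withdrawal criteria that everyone who stops the ointment becomes a LOCF case. That holds only if no later outcome is obtained, and the article says it will be sought.

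On standard errors, treating filled-in values as observed is a fault in principle. The simulations with equal dropout stayed near 5%, so no material inflation from that source is shown here.

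**Conclusion.** The point holds in this form: as the sole stated method, LOCF suits these outcomes poorly, because it ties the Day-7 result to when people leave. The rule is written in the article, so this is not a gap that an unseen analysis plan might fill. On the assumed course from 6 to 1.5, with dropout at Day 2 or 3, unequal dropout shifts the pain comparison by 0.18 to 0.51 VAS points with no true effect, against about 1 point detectable. At equal rates, a two-day difference in timing shifts it by 0.12 to 0.28 points on the linear assumption. The direction can go either way. With equal rate and timing only dilution remains, for example 1.05 read as 0.90. These sizes are illustrations; the existence of the problem needs only that symptoms improve over the week and that some patients leave early. The unstated precedence between retrieved and carried-forward values is a second, smaller matter of reconciliation.

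**What to change.** In Statistical analysis:

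1. Replace LOCF as the primary method with a mixed model for repeated measures on the daily scores, with terms for treatment, day, treatment-by-day, baseline, baseline-by-day and centre. Make the Day-7 treatment contrast the primary result.
2. State that all values obtained after withdrawal, including those after stopping the ointment, enter as observed and take precedence over any imputation. This reconciles the section with Data collection and management.
3. Keep LOCF as a sensitivity analysis. Add a delta-adjusted one, because the mixed model assumes data are missing at random and leaving because of pain or a skin reaction may strain that assumption.

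The withdrawal criteria need not be amended for this. The diary, the Day-7 visit and the retrieval effort are already planned, so no new data collection is needed and the sample size does not change. The cost is slightly more analysis work, plus the ethics and registry submissions that the Ethics section requires for a protocol revision. The change should be fixed before unblinding.
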